### Statistical precision

Given a fixed sample size of approximately 85 organizations (70% of 120 organizations) a sample size calculation is not relevant. Instead, we have calculated the level of statistical precision that we can expect given our fixed sample size. To calculate the expected statistical precision in the trial, an estimation of intra-class correlation coefficient (ICC) of measurements for individuals over time for the primary outcome is required. However, we have no mechanism to estimate the ICC due to the fact that no similar study with this population has been conducted (at least to our knowledge). Therefore, we calculated estimates of statistical precision for ICCs of 0.2, 0.3, 0.5, 0.7 and 0.8 based on a six-month trial period with 80% power, an estimated standard deviation of 1.0, significance of 0.05 (two-sided test), and 42 organizations per study group (total n = 85) [50]. Assuming the primary outcome data will be collected from all 85 organizations during the intervention period at six follow-up points (one per month), the time-averaged detectible differences (in standard deviation units) between the two groups is at best 0.35 (for ICC = 0.2), which increases with successively greater ICCs to 0.39 (for ICC = 0.3), 0.47 (for ICC = 0.5), 0.53 (for ICC = 0.7), and 0.56 (for ICC = 0.8).

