## RCT methods and design

### Study population and recruitment

Community-based HIV/AIDS organizations in Canada provide a number of programs and services to people living with or affected by HIV, which may include prevention initiatives, individual or group counseling/support, and community outreach and/or education. In addition, organizations in Canada are situated in diverse geographic settings ranging from dense urban settings to rural, northern, and/or remote settings, with some focused on specific at-risk populations and/or cultural or ethnic groups.

We will draw our sample from those organizations affiliated with the Canadian AIDS Society and from relevant provincial HIV/AIDS networks (*e.g.*, the Ontario AIDS Network), and send an organizational invitation to the executive director and management team (if applicable). The invitation will indicate that if they are interested in having their organization participate, access to SHARE will be provided to all interested staff. Given that SHARE is currently only provided in English, we will exclude organizations that do not have at least one key decision maker who is comfortable participating and corresponding in English.

To ensure clarity in our study recruitment, we will outline that consent from the executive director is required for the organization to participate. We will also indicate that we require one key organizational decision maker to fill out a brief survey measuring their intention to use research evidence (see the Outcomes section for more detail on the survey) on behalf of their organization at baseline and again at the completion of the trial. We will request that the executive director complete the survey, but will indicate that they can delegate to another manager provided the manager has a decision-making role about programs, services, and advocacy, and provided the manager does not include the conduct of research among their core responsibilities. Because the overall intent of the intervention is to support the use of research evidence in decisions about CBOs' programs, services, and advocacy, we deemed it most appropriate for the executive director (or another manager) to complete the survey because they would have the most impact on whether research evidence is used to inform decisions.

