### Data management and analysis

Data will be entered into SPSS 16.0 using unique identifiers that link each participant to their respective organizational identifier assigned during the randomization process. Analyses will be conducted by two members of the team ([name] and TB) and, during the analysis, all investigators -- except for one of us who is involved in the both the analysis and randomization (TB) -- will be blinded to the key linking the organizations to their unique identifiers.

We will treat both outcome measures as continuous variables and analyze the change in these measures over time using a two-way mixed effects linear repeated measures analysis of variance (ANOVA), which will assess the effects within groups, between groups, and over time with the latter as the main feature of interest. In addition, we will control for four variables -- province the organization is located in, size of organization (as measured by number full-time equivalent staff in the organization), number of participants that participated from each organization, and the number of clients served each year by the organization -- using analysis of covariance. For the analysis of the secondary outcome, we will also control for whether the key decision maker is full-time or part-time, and whether they have had research training in the past. Each of these variables may at least partially explain research use (*e.g.*, the amount of staff support an executive director or manager has may determine the extent to which they can spend time finding and using research evidence), and therefore adjusting for them will allow for a better assessment of the effects of the intervention. Moreover, as part of a secondary analysis, we will assess whether there is an interaction between each (entered as fixed factors) and the outcome measures. Given the likelihood that the distribution of the outcomes will be skewed, we will transform the data where necessary and possible, which may include adjusting the time period for which we calculate the mean number of logins/month/organization (*e.g.*, calculating the mean over two months) if the number of logins is low and there are insufficient data for analysis. We will also qualitatively compare the number of participants in the intervention and control groups that do not complete the follow-up survey, and attempt to assess if there are reasons for why they dropped out based on their baseline characteristics.

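### The stated detectable differences (0.35 to 0.56 SD, rising with ICC) ignore baseline, but the planned analysis is of change from baseline, for which they fall as ICC rises

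*Protocol article*

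**What the plan says.** Under Statistical precision, the protocol article treats the sample as fixed and reports detectable differences in place of a sample size calculation. The calculation is "based on a six-month trial period with 80% power, an estimated standard deviation of 1.0", with "significance of 0.05 (two-sided test), and 42 organizations per study group (total n = 85"). The ICC of repeated measurements is unknown, so five values are tried: "we calculated estimates of statistical precision for ICCs of 0.2, 0.3, 0.5, 0.7 and 0.8". The data counted are six monthly follow-up points in the intervention period, from every organization. The result is that "the time-averaged detectible differences (in standard deviation units) between the two groups is at best 0.35 (for ICC = 0.2"), and it is said to increase to 0.39, 0.47, 0.53 and 0.56 at ICC 0.3, 0.5, 0.7 and 0.8.

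Under Data management and analysis (RCT), the authors will "analyze the change in these measures over time using a two-way mixed effects linear repeated measures analysis of variance (ANOVA"). Of the within-group, between-group and over-time effects, they name the last as the main interest. The adjustment variables for the primary outcome are province, organization size, number of participants and number of clients. Baseline logins are not among them. The abstract describes the primary outcome as running from baseline to the end of the intervention, and Methods/design provides a two-month baseline with both arms on the self-serve version.

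**The concern.** The precision paragraph and the analysis paragraph appear to describe different contrasts. A follow-up average and a change from baseline respond to the ICC in opposite ways. When an organization's monthly values are strongly correlated, averaging six of them gains little, so a follow-up-only comparison gets worse. Subtracting baseline removes the stable part of the organization's usage, so a change comparison gets better.

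The authors say they cannot estimate the ICC, so a reader depends on how the figures move across the five values. If that direction is wrong for the planned analysis, the reader is misled at both ends: precision is overstated at low ICC and understated at high ICC. A null result could then be misjudged either way.

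**Working it through.** **Inputs, all from Statistical precision unless noted.** Two-sided alpha 0.05 (z = 1.960); power 80% (z = 0.8416); SD 1.0; n = 42 per arm; m = 6 follow-up months; r = ICC of 0.2, 0.3, 0.5, 0.7, 0.8. The two-month baseline is from Methods/design.

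**Assumptions.** Compound symmetry across all months (equal variances, equal correlation r), and a contrast of mean follow-up minus baseline. The number of baseline values, p, is not fixed by the text, so p = 2 and p = 1 are both shown. p = 2 covers both months or their average; p = 1 means one value with the SD of a single month.

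**Common formula.** Detectable difference = (1.960 + 0.8416) × √(2V/42) = 2.8016 × 0.2182 × √V = 0.6114 × √V.

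**Step 1: reproduce the plan.** For the average of six follow-up months, V = (1 + 5r)/6. At r = 0.2, V = 0.3333 and the difference is 0.6114 × 0.5774 = 0.353. At r = 0.8, V = 0.8333 and it is 0.6114 × 0.9129 = 0.558. All five published figures are matched within about 1.2%, so they belong to a follow-up-only comparison.

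**Step 2: change from baseline.** V = (1 − r)(1/6 + 1/p), that is (1 − r) × 2/3 for p = 2 and (1 − r) × 7/6 for p = 1. At r = 0.2 and p = 2, V = 0.5333 and the difference is 0.6114 × 0.7303 = 0.446. At r = 0.8 and p = 2, V = 0.1333 and it is 0.6114 × 0.3651 = 0.223.

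| ICC | Stated | Follow-up only | Change, p = 2 | Change, p = 1 |
|---|---|---|---|---|
| 0.2 | 0.35 | 0.353 | 0.446 | 0.591 |
| 0.3 | 0.39 | 0.395 | 0.418 | 0.552 |
| 0.5 | 0.47 | 0.467 | 0.353 | 0.467 |
| 0.7 | 0.53 | 0.529 | 0.273 | 0.362 |
| 0.8 | 0.56 | 0.558 | 0.223 | 0.295 |

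The follow-up-only and change columns cross at ICC 0.33 for p = 2 and at ICC 0.5 for p = 1. Below the crossing the stated figures are optimistic; above it they are pessimistic.

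**Step 3: power at the stated differences under the change analysis.** At r = 0.2 and p = 2, the standard error is 0.2182 × 0.7303 = 0.1594, so 0.35/0.1594 − 1.960 = 0.236 and power is 59%. At p = 1 the standard error is 0.2108, 0.35/0.2108 − 1.960 = −0.30 and power is 38%. At r = 0.8, power for 0.56 exceeds 99% in both cases.

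**Step 4: other readings of the over-time effect.** Last month minus baseline goes from 0.670 down to 0.335 (p = 2) or from 0.773 down to 0.387 (p = 1) as ICC goes from 0.2 to 0.8. A linear slope across the six months, expressed over its five intervals, goes from 0.654 down to 0.327. The size depends on the reading; the fall with ICC does not.

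**The case against.** A reader might infer that the published figures are miscalculated. They are not. They are right for their own formula and are openly labelled as time-averaged differences between groups over six follow-up points. For that quantity, both the best case at ICC 0.2 and the rise with ICC are correct. The fault lies in the match between this quantity and the planned analysis.

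It can also be said that the text never defines the contrast as mean follow-up minus mean baseline. The Outcomes section gives means for each period, and the ANOVA yields several effects. This stands as far as the exact replacement figures go, which is why a range is shown. It does not rescue the stated figures, because the over-time effect is named as the main interest and each version of it tried above falls with ICC.

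A third point is that adjusting follow-up for the two-month baseline mean would give 0.32, 0.32, 0.31, 0.25 and 0.21, so the protocol would be conservative at every ICC, with about 87% power for 0.35 at ICC 0.2. That is true, but the plan does not list baseline logins as a covariate. Under that analysis the direction does not strictly reverse: the figure is nearly flat and then falls.

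Finally, the number of organizations is set by the sector, no recruitment decision hangs on the paragraph, and the protocol promises 95% confidence intervals, which will show the precision achieved. This limits the harm but leaves the statement wrong for the planned analysis.

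**Conclusion.** The precision statement is wrong as written for the analysis the protocol describes. For change from baseline, the detectable difference falls from 0.45 to 0.22 SD (two baseline months) or from 0.59 to 0.30 SD (one baseline value) as ICC rises from 0.2 to 0.8. ICC 0.2 is the least favourable of the five values, and power there for 0.35 SD is 59% or 38%. These sizes rest on compound symmetry and on the assumed contrast.

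Two stronger readings are not supported. One is that the trial is underpowered overall. The documents give no basis for placing the ICC, and with two baseline months the change figures never exceed the stated worst case of 0.56. The other is that the sample size is inflated. The text says approximately 85, and 2 × 42 = 84 is exactly 70% of 120. The documents put no figure on losses from the English-language criterion, and provincial networks are also named as a source of organizations.

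**What to change.** Name the primary contrast explicitly, including how many baseline values enter it and how. Recompute the five detectable differences for that contrast, stating the correlation structure assumed. Delete the wording that 0.35 is the best case and the statement that the detectable difference increases with ICC. If the authors want to keep the present figures, they should label them as applying to a follow-up-only comparison and place them beside those for the planned analysis.

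As an optional improvement, the primary analysis could become a comparison of follow-up means adjusted for the two-month baseline mean. The variance factor is then (1 + 5r)/6 − 2r²/(1 + r), giving 0.32, 0.32, 0.31, 0.25 and 0.21 SD, smaller than the change analysis at every ICC. This must be declared as a change to the analysis, since it is not what the protocol now states.

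The cost is one rewritten paragraph, plus one sentence in the analysis section if the option is taken. No extra organizations or data are needed.

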## Qualitative methods/design

Given that this is the first RCT evaluating a KTE intervention for CBOs (at least to our knowledge) and the inherent limitations associated with measuring research use as an outcome, we will conduct a qualitative process study after the completion of the trial to explore the RCT findings in greater depth. The qualitative study will explore how and why the evidence service worked (or didn't work), determine how the 'full-serve' and 'self-serve' evidence services were used, including the degree of contamination between the intervention and control groups, and other factors that may have influenced their use (*e.g.*, the ease of use of SHARE).

### Sample

We will use a mixed method sequential nested sampling procedure whereby a larger sample is analyzed in one study (RCT), and a subset of the larger sample is selected for further inquiry in the second study [51]. Specifically, one key organizational decision maker from 15 organizations in each trial arm (n = 30) will be purposively sampled [52,53]. First, we will divide the organizations according to whether they received the 'full-serve' or 'self-serve' evidence service. Next, we will purposively sample in order to obtain a breadth of perspective by ensuring there is a mix with different outcomes from the trial (*i.e.*, varying levels of research use and intention to use research), and with varying size and location within the country. We have assumed a 70% response rate, which means that we should sample approximately 40 organizational key decision makers to achieve a sample size of 30.

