**Methods/design:**

We will conduct a two-arm randomized controlled trial (RCT), along with a follow-up qualitative process study to explore the findings in greater depth. All CBOs affiliated with Canadian AIDS Society (n = 120) will be invited to participate and will be randomized to receive either the 'full-serve' version of SHARE or the 'self-serve' version (a listing of relevant systematic reviews with links to records on PubMed and worksheets that help CBOs find and use research evidence) using a simple randomized design. All management and staff from each organization will be provided access to the version of SHARE that their organization is allocated to. The trial duration will be 10 months (two-month baseline period, six-month intervention period, and two month crossover period), the primary outcome measure will be the mean number of logins/month/organization (averaged across the number of users from each organization) between baseline and the end of the intervention period. The secondary outcome will be intention to use research evidence as measured by a survey administered to one key decision maker from each organization. For the qualitative study, one key organizational decision maker from 15 organizations in each trial arm (n = 30) will be purposively sampled. One-on-one semi-structured interviews will be conducted by telephone on their views about and their experiences with the evidence service they received, how helpful it was in their work, why it was helpful (or not helpful), what aspects were most and least helpful and why, and recommendations for next steps.

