### Data management and analysis

We will tape and transcribe all interviews, use N-Vivo 8 for data management of both the interview transcripts and document analysis, and use a constant comparative method for analysis [54-56]. Specifically, two reviewers will identify themes emerging from each successive wave of four to five interviews and iteratively refine the interview guide until we reach data saturation. This strategy will allow the reviewers to develop codes and broader themes in N-Vivo 8 that reflect the emerging and increasing levels of nuance that will inevitably result from the continuous checks that are involved in the constant comparative method [54,56]. We will also conduct member checking once analysis is completed (*i.e.*, we will send a brief, structured summary of what we learned from the interviews and invite comment on it). Finally, we will use the document analysis of the comments left in the user forum to help further our understanding of how participants engaged with the 'full-serve' version of SHARE.

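### Interview sample: approaching about 40 decision makers at the assumed 70% response gives about 28 interviews, not the stated 30

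*Protocol article*

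**What the plan says.** The interview target is the same in the Abstract (Methods/design) and in the Sample section under Qualitative methods/design: "one key organizational decision maker from 15 organizations in each trial arm (n = 30) will be purposively sampled". The Sample section then gives the allowance for non-response. It says "We have assumed a 70% response rate", and draws from this that "we should sample approximately 40 organizational key decision makers to achieve a sample size of 30".

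No formula is shown, and the 40 are not divided between the arms. Organizations are first separated by arm, then chosen to give a mix of trial outcomes, sizes and locations.

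Two other places bear on the point. The Statistical precision section gives the pool: "Given a fixed sample size of approximately 85 organizations (70% of 120 organizations", with 42 organizations per study group. The qualitative Data management and analysis section says that two reviewers will work through waves of four to five interviews and "iteratively refine the interview guide until we reach data saturation".

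**The concern.** The Sample section links three numbers: a response rate, a number to approach, and the number of interviews that should result. The second is presented as following from the first and third, so a reader can check it in one line, and it does not check. When a target is inflated for non-response, it is divided by the expected response rate. Here that gives a figure above 40.

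What is at stake is limited. The process study is the explanatory half of a sequential mixed-methods design, and its 15 interviews per arm have to cover a range of organizations and results. A recruitment number that is expected to fall short of its own target should be put right before invitations go out, though nothing in the randomized comparison depends on it.

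**Working it through.** **Inputs, all from the protocol article**

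- Target: 15 interviews per arm, 30 in total (Abstract; Sample).
- Assumed response: 70%, so non-response is 30% (Sample).
- Stated number to approach: approximately 40 (Sample).
- Pool: about 42 organizations per arm (Statistical precision).

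**Step 1. Try to reproduce the stated 40**

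Number to approach = target / response rate = 30 / 0.70 = 42.9, so 43. The stated figure is not reproduced.

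Two other routes do lead to about 40:

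- Multiplying by one plus the non-response rate: 30 × 1.3 = 39. By arm, 15 × 1.3 = 19.5, so 20, and twice that is 40.
- Rounding 42.9 to the nearest ten gives 40.

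The text does not allow a choice between them, and both fall short of the target.

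**Step 2. Run the stated figures forward**

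- Expected interviews = 40 × 0.70 = 28, two below target.
- With an equal split of 20 and 20 (an assumption), 20 × 0.70 = 14 per arm, one below target in each.
- Response rate needed for 30 from 40 = 30 / 40 = 75%.
- Reading approximately 40 as anything up to 42 does not help: 42 × 0.70 = 29.4.

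**Step 3. The split by arm**

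Each arm needs 15 / 0.70 = 21.4 approaches for an expected 15. Two arms need 42.9, which is more than 40. So under any split of 40, at least one arm has an expected yield below 15. That both arms fall short follows only for splits close to equal.

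**Step 4. Corrected number**

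- In total: 43 approaches, 43 × 0.70 = 30.1 expected.
- By arm: 22 approaches, 22 × 0.70 = 15.4 expected; 44 in all, 30.8 expected.
- Feasibility: 22 is well below the roughly 42 organizations available per arm.

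**Step 5. Chance of reaching the target in a single batch**

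This step adds assumptions that the article does not make: each person approached accepts independently with probability 0.70, nobody else is approached afterwards, and the arms are approached equally. The figures are binomial tail probabilities.

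| Approached | At least 30 in total | At least 15 in one arm | At least 15 in both arms |
|---|---|---|---|
| 40 (20 per arm) | 0.31 | 0.42 | 0.17 |
| 44 (22 per arm) | 0.67 | 0.67 | 0.45 |

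Even 44 approaches in one batch would fill both arms less than half the time. Correcting the number is therefore not enough to secure 15 per arm; that also needs further approaches when an arm falls short.

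**The case against.** The strongest defence is that the word approximately signals a loose planning figure and that nothing of substance hangs on it. The article rounds loosely elsewhere: 70% of 120 is 84, given as approximately 85. The sample is purposive, interviewing is guided by saturation as well as by the count of 30, nothing limits approaches to 40, and about 42 organizations per arm are available. A shortfall of two can be made up by approaching a few more.

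Most of this stands, and it is why the point is minor. It does not make the numbers agree. Rounding a recruitment number down moves it away from its target, and the article still states 30 as the result. The waves of interviews are described for analysis and for refining the interview guide, not as a rule for sending more invitations.

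Four stronger readings are tempting, and the documents do not support them:

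- A reader might infer that the authors multiplied by 1.3 instead of dividing by 0.70. No formula is given, and rounding down explains 40 equally well.
- A reader might infer that both arms are expected to miss 15. That needs a near-equal split, which is plausible but not stated.
- A reader might infer that the shortfall leaves planned sampling cells thin. The Sample section seeks a mix and sets no cells or quotas.
- A reader might take the 31% and 17% chances as the plan's chances of success. They describe one fixed batch of independent invitations with no top-up, which the article does not specify.

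**Conclusion.** The point holds as a minor arithmetic correction. On the article's own figures, about 40 approaches at 70% response are expected to give about 28 interviews, against a stated 30. This needs no outside assumption. The figure of 14 per arm rests on an equal split, and the probabilities rest on the single-batch assumptions given with them. The cause of the discrepancy is unknown.

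The consequence is confined to the qualitative process study and amounts to about two interviews, which the available pool can supply. The primary and secondary outcomes, the precision calculation and the error rate of the randomized trial are not affected.

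**What to change.** In the Sample section, replace approximately 40 with about 43 or, better, with 44 (22 per arm), since the target is set per arm. Add that further organizations will be approached in either arm until 15 have accepted. This costs one sentence and three or four more invitations at the outset, plus any needed to top up an arm. The number of interviews can still be held at 30 by stopping invitations in an arm once 15 have accepted.

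Alternatively, keep 40 and state the expected yield as about 28. The 30 in the Abstract and the Sample section should then be changed to match, or described as a target that may need further approaches.
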